#### Randomization/blinding

Subjects agreeing to participate will be randomly allocated to the intervention (n = 155) or control group (n = 155). Randomization will be stratified by age, gender, prediabetes and FINDRISC score, with the aim of obtaining an equal distribution of participants between the two groups. Spouses will be randomized to the same group, and spouses not fulfilling the inclusion criteria will be invited to participate in the study by supporting their husband or wife.

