### Economic evaluation

Cost-effectiveness analysis will be performed from patient, health care and societal perspectives. In the societal perspective, all costs are included irrespective of who is burdened by them, while the health care perspective is only concerned with costs burdening the health care sector. The patient perspective focuses on the costs that the patients have to bear to change their lifestyle habits through the intervention. The societal perspective is generally preferred, although a health care perspective supplies additional (affordability) information and can strengthen conclusions based on the societal perspective. The results will be presented in terms of incremental cost-effectiveness ratios (ICERs), which show the change in costs for an incremental benefit [19]. To determine the cost-effectiveness of the intervention, ICERs will be calculated for all statistically significant outcomes. In cost utility analysis, utility values will be calculated using the EQ-5D questionnaire which provides the health related quality of life as quality adjusted life years (QALY).

We will perform economic evaluation in two different time horizons; short-term (within-trial) and long-term. Within-trial economic evaluation will only focus on the trial cost data and the outcomes. For long-term duration, we will develop a decision analytic model based on the outcome of the trail. This will be done by extrapolating the secondary clinical outcomes (BMI, blood pressure, lipid profile) to predict future disease events such as CVD, diabetes and diabetes-related complications. Each disease event will have a future cost and QALY. Future costs and effects will be discounted by 3% per year, but we intend to perform sensitivity analyses on other rates [58]. We will analyze uncertainty by both one-way and multi-way sensitivity analysis, and also by non-parametric bootstrapping. We will calculate 95% confidence intervals for the ICERs.

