#### Cost-effectiveness analysis

It is assumed that the point estimates for differences in mean cost and QALY between the intervention and control groups will be 1000 SEK and 0.18 QALY, respectively, with differences in the SDs for cost and QALY of 5000 SEK and 0.26 QALY, respectively. The sample size of 260 (130 per group) provides 0.84 power, assuming that the WTP is 1.3 million SEK [64,65].

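### The economic evaluation names the ICER and its confidence interval but no net-benefit measure; the ratio does not separate QALY gain from QALY loss if the within-trial difference is near zero

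*Protocol article*

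**What the plan says.** Under Economic evaluation, the protocol article sets the scale of the result: "The results will be presented in terms of incremental cost-effectiveness ratios (ICERs), which show the change in costs for an incremental benefit". It adds a condition: "To determine the cost-effectiveness of the intervention, ICERs will be calculated for all statistically significant outcomes". The next sentence brings in QALYs from the EQ-5D for a cost-utility analysis, but does not say whether the significance condition applies to them. Uncertainty is handled in two sentences. One reads "We will analyze uncertainty by both one-way and multi-way sensitivity analysis, and also by non-parametric bootstrapping"; the other, placed directly after it, reads "We will calculate 95% confidence intervals for the ICERs". The construction of that interval is not given. Net benefit, the cost-effectiveness plane and acceptability curves are not mentioned.

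The only threshold is in the power statement, under Sample size and power calculation, Cost-effectiveness analysis: "The sample size of 260 (130 per group) provides 0.84 power, assuming that the WTP is 1.3 million SEK". The assumed effects there are "differences in mean cost and QALY between the intervention and control groups will be 1000 SEK and 0.18 QALY, respectively". For the spread, the article gives SD figures of 5000 SEK for cost and 0.26 for QALYs, without making clear whether these are per-arm values.

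**The concern.** An ICER is the cost difference divided by the QALY difference, and the division loses the sign. A programme that costs more and loses QALYs has a negative ICER, and so does one that saves money and gains QALYs. Both rank below any positive threshold. When plausible values of the QALY difference lie on both sides of zero, the ratio jumps between plus and minus infinity, and ordering bootstrap ratios to read off percentiles mixes good replicates with bad ones.

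The fourth aim of the study is to establish cost-effectiveness, and the abstract addresses the results to health care providers and policy makers. If the within-trial QALY difference is small, an ICER interval set beside 1.3 million SEK could look favourable when the data show no benefit, or even a loss. In addition, a power at a stated WTP is naturally the power of a net-benefit analysis, and the Economic evaluation section names no such analysis.

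**Working it through.** **Inputs.** From the power statement: cost difference 1000 SEK, QALY difference 0.18, SDs 5000 SEK and 0.26 QALY, 130 per group, WTP 1.3 million SEK, stated power 0.84. Assumptions of this check: the SDs are per-arm, person-level SDs (the wording is ambiguous), data are normal, cost and QALY are uncorrelated, and tests are two-sided at 5%.

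**The plan's own figure.** Net monetary benefit is NMB = WTP × QALY difference − cost difference.

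- Planned NMB = 1,300,000 × 0.18 − 1000 = 233,000 SEK
- SD = √(5000² + (1,300,000 × 0.26)²) ≈ 338,000 SEK
- SE = 338,000 × √(2/130) ≈ 41,900 SEK
- Ratio = 233,000/41,900 ≈ 5.56, so power ≈ Φ(5.56 − 1.96) > 0.999

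The stated 0.84 is not reproduced. Varying the correlation from −1 to 1 does not change this. That is a separate matter. Here it means only that the WTP suggests a net-benefit calculation, while the figure itself does not confirm one.

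**Standard errors.** QALY difference: 0.26 × √(2/130) = 0.0322. Cost difference: 5000 × √(2/130) = 620 SEK. The planned 0.18 is 0.18/0.0322 = 5.6 standard errors from zero, so the denominator stays clear of zero and the ratio behaves well.

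**How near zero might the within-trial difference be?** The EQ-5D is taken at 0, 3 and 6 months. With equal baselines, linear interpolation and a constant utility difference d from month 3, the QALY difference is 0.25 × d/2 + 0.25 × d = 0.375d. A difference of 0.18 within the trial would need d = 0.18/0.375 = 0.48. An illustrative d of 0.05 (an assumption, not a figure in the article) gives 0.019 QALY, or 0.6 standard errors. About 28% of estimates would then show a QALY loss.

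**Why the ratio misleads.** Take an extra cost of 1000 SEK.

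| QALY difference | ICER (SEK per QALY) | NMB at 1.3 million SEK |
|---|---|---|
| +0.02 | +50,000 | 26,000 − 1000 = +25,000 |
| −0.02 | −50,000 | −26,000 − 1000 = −27,000 |

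Both ICERs are far below the threshold; only NMB tells them apart. The ICER exceeds 1.3 million SEK only if the QALY difference lies between 0 and 1000/1,300,000 = 0.00077. With no true effect, that has probability Φ(0.00077/0.0322) − 0.5 ≈ 0.0095. The ICER point estimate is therefore below the threshold in about 99% of such trials, and about half of those show a QALY loss.

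**Simulation, no significance filter.** The interval is a percentile interval of the ratio, with 130 per group. Ranges cover the separate runs.

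| True QALY difference | QALY SD | Cost difference (SEK) | Upper ICER limit < 1.3 million | Lower NMB limit > 0 |
|---|---|---|---|---|
| 0 | 0.26 | 1000 | 99.7–100% | about 1–2.6% |
| −0.02 | 0.26 | 1000 | 99–100% | under 1% |
| −0.05 | 0.26 | 1000 | about 100% | under 1% |
| 0 | 0.13 | 1000 | 86–88% | about 2–2.5% |
| 0 | 0.05 | 1000 | 31–33% | about 2% |
| 0 | 0.26 | 5000 | 26–28% | about 2% |
| 0.18 | 0.26 | 1000 | 100% | about 100% |

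**With the significance filter applied to QALYs.** With no true effect, an ICER is calculated in about 5% of trials. Practically all of these are below the threshold, and about half are for a QALY loss. With a true loss of 0.05 (SD 0.26), about 34% of trials have a significant QALY loss and an ICER interval wholly below the threshold.

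**The case against.** A reader might infer that the plan judges cost-effectiveness by comparing a bootstrap ICER interval with 1.3 million SEK, so that an ineffective programme would almost always be declared cost-effective. The documents do not support that.

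- No rule compares the ICER or its limits with a threshold. The 1.3 million SEK appears only in the power statement.
- The interval is not said to be a percentile interval. Bootstrapping and the interval are in adjacent sentences, and the method is left open. A Fieller-type interval would be bounded only when the QALY difference is significant, so it would be unbounded in about 95% of null trials. That is honest about the uncertainty, though it gives little to decide on.
- If the limit to significant outcomes covers QALYs, only about 5% of null trials yield an ICER at all.
- The zero effect is this review's scenario. The plan's own 0.18 is well clear of zero.
- Not naming net benefit alongside a WTP-based power is a mismatch, not a contradiction. A condensed article may leave supporting displays to a fuller plan.

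All of this stands, and it narrows the point. What remains is that the article does choose its statistic, the ICER with a confidence interval, and that statistic does not carry the sign of the effect. The significance filter does not restore the sign either: it passes significant losses and significant gains alike.

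**Conclusion.** The point holds in a limited form. The Economic evaluation section rests the result on a ratio and its interval and names no net-benefit measure, while the power statement uses a WTP that fits one. The weakness matters only if the within-trial QALY difference is small relative to its standard error of about 0.032. At 0.18 it does not arise.

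The near-100% figure against about 2.5% for net benefit illustrates what could happen. It is not a property of the plan as written. It depends on a percentile interval, a cost difference of 1000 SEK, per-arm SDs, no correlation, no QALY effect, no significance filter, and a reader who sets the interval beside the threshold. It falls to roughly 26 to 33% with a QALY SD of 0.05 or a cost difference of 5000 SEK. The change is worth making because the alternative is clearly better and costs almost nothing.

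**What to change.** In Economic evaluation, make incremental net monetary benefit at 1.3 million SEK per QALY, with its bootstrap 95% confidence interval from the same replicates, the measure of uncertainty in place of the interval for the ICER. Add the cost-effectiveness plane with the share of replicates in each quadrant, and an acceptability curve over a range of WTP values. Keep the ICER as a point estimate, labelled dominant or dominated where the signs require it. The power statement then has a named analysis to refer to.

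The cost is a few sentences, with no extra participants, measurements or resampling. The small downside is that the net-benefit result is tied to a stated WTP, which the acceptability curve addresses.

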### Process evaluation

To assess adherence to the intervention protocol, attendance at group counseling sessions and exercise sessions will be registered, as will accomplishment of individual activities (*e.g.* smart goal sheet, *FaR*).

### Cultural adaptation

Special emphasis will be placed on adapting the intervention to the cultural norms, beliefs and traditions of the participants from the beginning to the end of the study period. In order to achieve successful lifestyle change, gender-specific education exercise groups will be offered and physical activity sessions will be adapted to the preferences of the participants [17,18]. Moreover, the intervention will be provided by a multidisciplinary team comprising a health coach, nurses, a physiotherapist and a doctor, and mediates behavioral change and self-empowerment that has been shown to improve the response to lifestyle change in ethnic minority groups [18].

Study materials, including the informed consent form, participant information, food booklets, and newsletters, will be translated into Arabic. Questionnaires only available in English or Swedish will be translated into Arabic according to WHO guidelines for translating instruments [62] and will be administered by a health care professional who can speak both Swedish and Arabic.

## Statistical analysis

### Sample size and power calculation

#### Fasting glucose

From the baseline study and earlier intervention studies on Arabic participants, we estimate a standard deviation (SD) of fasting glucose of 0.6 [12,63]. Based on earlier studies, we assume that the true difference between the intervention and control group means is 0.22 mmol/L [12,63]. We will be able to reject the null hypothesis that the population means of the intervention and control groups are equal with a power of 0.86.

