**Methods/design:**

In this randomized controlled trial, 308 participants (born in Iraq, living in Malmö, Sweden and at high risk of type 2 diabetes) will be allocated to either a culturally adapted intervention or a control group. The intervention will consist of 10 group counseling sessions focusing on diet, physical activity and behavioral change over 6 months, and the offer of exercise sessions. Cultural adaptation includes gender-specific exercise sessions, and counseling by a health coach community member. The control group will receive the information about healthy lifestyle habits provided by the primary health care center. The primary outcome is change in fasting glucose level. Secondary outcomes are changes in body mass index, insulin sensitivity, physical activity, food habits and health-related quality of life. Measurements will be taken at baseline, after 3 and 6 months. Data will be analyzed by the intention-to-treat approach. The cost-effectiveness during the trial period and over the longer term will be assessed by simulation modeling from patient, health care and societal perspectives.

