### Participants

#### Eligibility criteria

Participants are recruited from the MEDIM baseline study that by December 2012 had included 1398 men and women aged 30 to 75 years born in Iraq, and in whom a glucose tolerance test was performed and sociodemography and lifestyle was characterized. In total 40% of the participants are estimated to be at risk of diabetes either by having prediabetes (IFG, IGT or IGR) or by their constellation of risk factors according to FINDRISC scores [21] resulting in a moderate (17%) to high risk (33%) to develop diabetes within the next decade. Thus we will have an eligible population of 1398*0.40 = 560 individuals, of whom 60% or 336 are estimated to finally agree to participate in the study. The participation rate is based on experiences from an intervention study of Arabic women, which had a participation rate of 62% [17]. In the baseline study 315 Iraqi individuals had a moderate risk (i.e. an estimated 10 year incidence rate of diabetes of 17%) [21] and 275 individuals had a high risk (i.e. an estimated 10 year incidence rate of diabetes of 33%) [21]. Based on a mean time of two years from baseline to the start of the study, we estimate that 26 individuals may have developed diabetes during this period. They will consequently be excluded from the study. Based on a drop-out rate of about 16%, we estimate that of the 310 individuals that initially participated 260 will complete the study (130 per group).

Inclusion criteria were being born in Iraq, age 30 to 75 years and high risk of diabetes as measured by

A. IFG, IGT or IGR identified by an oral glucose tolerance, plasma glucose (glc) at fasting (f-glc) and at 2 hours (2-h glc) during glucose tolerance test:

•  IFG: f-glc 6.1-6.9 mmol/L (110.125 mg/dL) and 2-h glc <7.8 mmol/L (<140 mg/dL)

•  IGT: f-glc < 6.1 mmol/L (<110 mg/dL) and 2-h glc 7.8-11.0 mmol/L (140.199 mg/dL)

•  IGR: f-glc . 6.9 mmol/L (.125 mg/dL) and 2-h glc 7.8-11.0 mmol/L (140.199 mg/dL)

B. or by Finish diabetes risc score (FINDRISC) with over 10% risk of diabetes in 10 years.

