### Univariate and multivariate analysis

The trial data will be analyzed on an intention-to-treat basis. Bivariate and multivariate analyses will assess the effects of the intervention (compared to controls) on fasting glucose level, weight, physical activity level and dietary intakes, with adjustment for age and gender, and will identify factors that can predict beneficial and non-beneficial responses to the intervention (*e.g.* baseline physical activity, motivation, attitude, adherence to the intervention). Continuous data will be analyzed with paired Student’s t-tests and linear regression, and categorical variables with chi square tests and logistic regression with 95% confidence intervals.

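### The printed inputs give a power of 0.84 at 130 per group, not 0.86; the SD is that of the glucose level while the outcome is change, and baseline glucose is not a named covariate

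*Protocol article*

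**What the plan says.** All references are to the protocol article.

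- **Power statement** (Sample size and power calculation, Fasting glucose): "we estimate a standard deviation (SD) of fasting glucose of 0.6"; "the true difference between the intervention and control group means is 0.22 mmol/L"; and the null hypothesis that "the population means of the intervention and control groups are equal with a power of 0.86" can be rejected. The paragraph gives no sample size, significance level or sidedness. The cost-effectiveness paragraph that follows does name its sample size, 260 (130 per group).
- **Enrolment**: the abstract has "308 participants". Eligibility criteria expects that "of the 310 individuals that initially participated 260 will complete the study (130 per group"), after about 16% drop-out. Randomization/blinding allocates 155 to each arm, which is 310.
- **Outcome**: in the abstract, "The primary outcome is change in fasting glucose level".
- **Analysis** (Univariate and multivariate analysis): effects on several outcomes, including the fasting glucose level, are assessed "with adjustment for age and gender". The methods listed for continuous data are paired t-tests and linear regression. Baseline glucose is not named as a covariate, although Table 1 shows fasting plasma glucose measured at baseline, 3 and 6 months.

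**The concern.** Three things do not line up.

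1. The stated power cannot be tied to a sample size. The article offers three totals (260, 308, 310), and the printed inputs do not return 0.86 to two decimals with any of them.
2. The calculation uses the spread of a level, while the declared outcome is a change. These are different quantities unless the correlation between baseline and 6 months is exactly 0.5.
3. The named adjustment set leaves out the covariate most directly related to the outcome. Without it, the power of a change-score analysis depends on a correlation that the article does not report.

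At stake are the traceability of the primary power claim and some efficiency that could be had from data already collected. The validity of the randomized comparison is not at stake.

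**Working it through.** **Inputs from the article.** SD 0.6 mmol/L, difference 0.22 mmol/L, 130 completers per group, 155 per group randomized (154 if the abstract's 308 is split equally).

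**Assumptions.** Two-sided 5%, in line with the 95% intervals in the analysis section; independent participants; for the change calculations, an SD of 0.6 at both visits and a correlation r that the article does not give.

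**Step 1: the plan's own figure.** By the normal approximation, power = Φ(Δ / (SD·√(2/n)) − 1.96).

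For n = 130: the standard error is 0.6 × √(2/130) = 0.0744; 0.22 / 0.0744 = 2.956; Φ(0.996) = 0.840.

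| n per group | Normal | t-test |
|---|---|---|
| 130 | 0.840 | 0.838 |
| 154 | 0.896 | 0.894 |
| 155 | 0.898 | 0.896 |

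One-sided 5% at 130 per group gives 0.905, so sidedness does not recover 0.86. Solving for n at a power of 0.86 gives 138 per group (276 in total), a number that the article does not contain.

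**Step 2: can rounding explain 0.86?** At 130 per group, an SD of 0.58 gives 0.864 and 0.59 gives 0.852. An SD near 0.583, which prints as 0.6, gives 0.86. A difference of 0.225 with SD 0.6 gives 0.856. So rounding could account for the gap.

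**Step 3: enrolment.** 310 × 0.84 = 260.4, and 260/308 = 0.844 (15.6% lost). Both totals fit 260 completers and about 16% drop-out, so this arithmetic does not settle which is meant. The effect on power is about 0.002 (0.896 against 0.898).

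**Step 4: level against change.** The SD of an unadjusted change is 0.6·√(2(1 − r)), which equals 0.6 only when r = 0.5. With baseline glucose as a covariate, the residual SD is 0.6·√(1 − r²). Power at 130 per group (normal approximation):

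| r (assumed) | SD of change | Power, change score | Residual SD, baseline-adjusted | Power, baseline-adjusted |
|---|---|---|---|---|
| 0.3 | 0.710 | 0.705 | 0.572 | 0.873 |
| 0.4 | 0.657 | 0.770 | 0.550 | 0.897 |
| 0.5 | 0.600 | 0.840 | 0.520 | 0.927 |
| 0.6 | 0.537 | 0.911 | 0.480 | 0.959 |
| 0.7 | 0.465 | 0.968 | 0.428 | 0.985 |

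**Step 5: why the covariate is safe.** The adjusted variance divided by the change-score variance is (1 − r²) / (2(1 − r)) = (1 + r)/2, which is never above 1. Against a plain comparison of 6-month levels the ratio is 1 − r², also never above 1. The only cost is one degree of freedom out of about 258.

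**The case against.** The strongest reply has three parts.

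**The power gap is trivial.** It is about 2 points, and the SD is printed to one digit. Over the full rounding range (SD 0.55 to 0.65, difference 0.215 to 0.225), power at 130 per group runs from about 0.76 to 0.91, so the printed inputs cannot show that 0.86 is wrong. Both figures exceed 0.80. This stands: a reader might infer that 0.86 has no basis, and the article does not support that. What remains is that the printed numbers give 0.84 and the paragraph states no sample size.

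**No loss of power is shown.** A reader might infer from the level-versus-change mismatch that the trial is underpowered. That does not follow. Power for a change score falls only if r is below 0.5, and above 0.5 it exceeds the figure from the printed inputs. The analysis section also names the glucose level as the variable analysed, and for a comparison of 6-month levels 0.6 would be the matching SD. Whether the cited sources gave the SD of a level or of a change cannot be checked here. All of this stands. The remaining fault is that the wording of the SD and the wording of the outcome differ and the article does not reconcile them.

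**The covariate list may be a summary.** A fuller analysis plan may add baseline glucose. Randomization is stratified by prediabetes, which limits imbalance at baseline, and change scores are unbiased under randomization. So it would be too strong to say that the trial's model excludes baseline glucose or that nothing protects the comparison. But the article does state an adjustment set, and a plan that is not shown does not alter what it states.

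**Conclusion.** The point holds in a limited form.

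- From the printed inputs, power is 0.84 at 130 per group and about 0.90 at 154 or 155 per group, assuming a two-sided 5% test. No printed sample size gives 0.86 to two decimals. The 2-point gap is minor and may be rounding.
- The enrolment totals of 308 and 310 conflict. The difference has almost no effect on power.
- The SD is described for the level and the outcome is defined as change. Change-score power is therefore undetermined, from 0.70 to 0.97 for assumed correlations of 0.3 to 0.7. Underpowering is not shown.
- The adjustment set stated in the article can be improved at no real cost. Adding baseline fasting glucose gives about 0.87 to 0.98 over the same range and makes power far less dependent on the unknown correlation.

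All figures assume independent participants and an SD of 0.6 at both visits. Any correlation between spouses, who are allocated together, or between members of a counseling group would lower them; that is a separate matter and is not quantified here.

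**What to change.** 1. Use one enrolment total, 308 or 310, in the abstract and the methods.
2. Put the sample size, significance level and sidedness beside the primary power statement. Either restate it as 0.84 for 130 per group (two-sided 5%, SD 0.6, difference 0.22 mmol/L) or print the unrounded inputs that give 0.86.
3. Say whether 0.6 is the SD of the level or of the change. If it is the SD of the change, give its source; if it is that of the level, give the assumed correlation.
4. Make the primary analysis a between-group linear model of 6-month fasting glucose on arm, with baseline fasting glucose added to age and gender. Keep paired t-tests, if wanted, for describing change within an arm.

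The cost is wording only: no more participants, visits or measurements. If the power is restated, the headline figure falls by about 2 points, and the covariate more than recovers this at every correlation in the table.
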